### Interim analyses {21b}

After 600 (40%) patients enrolled per group, we will conduct an interim analysis of the primary outcome to assess whether the study is working as expected. The O’Brien-Fleming boundaries at the interim analysis for efficacy and futility are 3.35 and −3.35, respectively. If the futility boundary is crossed, indicating that we have failed to improve patient mobility, then the trial will be stopped, because if we cannot improve mobility, there is no reason to think we could improve the other outcomes. On the other hand, if we cross the boundary for efficacy, we will still continue the trial in order to assess the important secondary outcomes which are the basis for our power calculation. We do not expect to assess outcomes such as discharge disposition until the end of the trial. The one exception is that halfway through the trial (at 18 months) we will compare the safety outcomes of falls and falls with injury. The DSMB will review these results to determine if there are significant risks to continuing the study.

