Role of sponsor {5c}	NIA will monitor progress of the study and will convene the Data Safety Monitoring Board (DSMB). The PI will provide NIA with interval reports of study progress with enrollment, dropouts and safety events. If there are unexpected delays, NIA may offer advice or support. NIA will convene the DSMB and ensure it has regular meetings as determined by their charter. Data will be provided to the DSMB by the study statistician. NIA may stop the study at any point if it determines there are serious safety concerns or for evidence of futility. The study statistician will prepare an analysis for futility once 40% of the patients have reached Time 2.

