### Sample size {14}

A sample size of 3000 has >99% power to detect a difference in SPPB change as small as 0.54 points (the MCID) between the two groups at a two-sided alpha of 0.05, assuming a common SD of 2.7 for the SPPB change, 20% non-compliance, 10% dropouts, and an interim analysis. The estimates for MCID and SD are based on observation of older acute care medical patients [43, 44]. Using these same assumptions, the power is still 92% for detecting a smaller difference of 0.35. Therefore, we expect ample statistical power for analyzing the primary outcome. The main reason for selecting this sample size is to ensure that the analyses of important secondary outcomes are not underpowered. The most important of these is discharge disposition, because even a small absolute difference in the number of patients discharged to home, as opposed to a skilled nursing facility, is clinically important. We will be able to detect a 7% difference in discharge to home vs. SNF with 98% power.

For other binary secondary outcomes (a combination of venous thromboembolism, pneumonia and falls, 30-day mortality, or 30-day readmission), the study will have 85% power to detect a 33% reduction assuming an 8% rate in the control group. Because these outcomes are not contingent on patient cooperation, we anticipate no dropouts. For secondary continuous outcomes such as length of stay, assuming 20% non-compliance rate, the power to detect a 4-h difference (0.167 days) is 95%.

Regarding the cost analysis, there is no accepted way of doing a power calculation. However, we tried adding $300 (an approximation of the cost of the intervention) to the costs of each of 1500 patients drawn randomly from a sample of 3000 Cleveland Clinic medical inpatients over the age of 65 with an AM-PAC 6-Clicks score between 16 and 20. We then performed a *t*-test on the log-transformed costs, as described in the economic analysis section, and we were able to detect the increase with a p-value of 0.03, indicating that should the intervention increase costs by an amount equal to the cost of the intervention, we should be able to identify it. Similarly, if the intervention decreases total costs by $300 or more (not including the costs of the intervention), we should have sufficient power to detect it.

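### The interim boundary of Z = −3.35 is labelled futility but is a harm bound, so the stated rule does not stop the trial when mobility fails to improve

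*Protocol article*

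**What the plan says.** **Timing and boundaries.** The section *Interim analyses {21b}* sets one look at the primary outcome: "After 600 (40%) patients enrolled per group, we will conduct an interim analysis of the primary outcome". The O'Brien-Fleming "boundaries at the interim analysis for efficacy and futility are 3.35 and −3.35, respectively".

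**Stated meaning.** "If the futility boundary is crossed, indicating that we have failed to improve patient mobility, then the trial will be stopped". The reason given is that, without a gain in mobility, no gain in the other outcomes is to be expected. A crossing of the upper boundary does not stop the trial, which continues for the secondary outcomes.

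**Elsewhere.** *Role of sponsor {5c}* also describes the 40% look as a futility analysis, with a different trigger: "The study statistician will prepare an analysis for futility once 40% of the patients have reached Time 2". The same section lets the sponsor stop the study at any time for safety or futility. The section on the data monitoring committee {21a} leaves stopping rules and guidelines to a DSMB charter. The article gives no other numeric futility rule.

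**The concern.** A futility rule stops a trial whose interim result makes eventual success unlikely. A bound of Z = −3.35 on the treatment comparison instead requires strong evidence that the intervention is worse than control. An intervention with no effect gives an interim Z near 0, far from that bound. The number and the meaning attached to it therefore disagree within one paragraph.

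At stake is the declared purpose of the look. Because an efficacy crossing does not stop the trial, the only stop that this numeric rule can trigger is for marked harm. In the case that the paragraph describes, where mobility is not improved, the rule almost never acts.

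**Working it through.** **Inputs**
- Alpha: the *Sample size {14}* comparison is made "between the two groups at a two-sided alpha of 0.05".
- Variability and losses: "assuming a common SD of 2.7 for the SPPB change, 20% non-compliance, 10% dropouts, and an interim analysis".
- Total 3000, hence 1500 per group. MCID 0.54 points; smaller effect considered 0.35 points.
- Interim at 600 per group, information fraction t = 600/1500 = 0.40. Allowing for 10% dropout, 600 × 0.9 = 540 evaluable per group at the look and 1500 × 0.9 = 1350 at the end.

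**1. Reproducing the plan's figure.** Lan-DeMets O'Brien-Fleming-type spending with 0.025 per side at t = 0.40:

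- spent per side = 2 × [1 − Φ(2.2414/√0.40)] = 2 × [1 − Φ(3.544)] = 0.000394
- Z = Φ⁻¹(1 − 0.000394) = 3.357

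The stated 3.35 has a nominal p of 0.00040 per side (0.0008 two-sided), so the figure is reproduced. The classical two-look O'Brien-Fleming bound would be ±3.11, and spending a total of 0.05 split over two sides gives ±3.10; neither matches. The stated pair is therefore the two-sided 0.05 rejection pair, and its lower member rejects the null in favour of harm.

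**2. What −3.35 means in SPPB points.** SE = 2.7 × √(2/n):

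| Evaluable per group | SE | Observed difference needed (−3.35 × SE) |
|---|---|---|
| 600 | 0.156 | −0.52 |
| 540 | 0.164 | −0.55 |

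That is about one MCID (0.54) in the wrong direction.

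**3. Chance that the rule stops the trial.** P(stop) = Φ(−3.35 − δ/SE), where δ is the true difference (negative means harm):

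| True δ | 600 per group | 540 per group |
|---|---|---|
| 0 | 0.04% | 0.04% |
| −0.27 | 5.3% | 4.4% |
| −0.35 | 13% | 11% |
| −0.54 | 55% | 47% |

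With no effect, 0.04% is about 1 trial in 2,500.

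**4. A flat interim result.** At interim Z = 0, conditional power under the current trend is 1 − Φ(1.96/√0.60) = 1 − Φ(2.530) = 0.6%. The stated rule says to continue.

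**5. Cost of one alternative, Z ≤ 0 (an illustration, not in the documents).** Under no effect, P(stop) = Φ(0) = 50%. For a true benefit δ, P(stop) = Φ(−δ/SE) with SE = 0.164. The power loss comes from the bivariate normal for interim and final Z with correlation √0.40, 1350 evaluable per group and a final critical value of 1.96. The effects 0.432 and 0.28 are 0.54 and 0.35 diluted by 20% non-compliance (0.54 × 0.8 and 0.35 × 0.8).

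| True effect | P(stop) at Z ≤ 0 | Power without the bound | Power with it | Loss (points) |
|---|---|---|---|---|
| 0.432 | 0.4% | 98.6% | 98.3% | 0.3 |
| 0.35 | 1.7% | 92.0% | 91.3% | 0.7 |
| 0.28 | 4.4% | 76.9% | 75.9% | 1.0 |

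At a true benefit of 0.10 points, the bound would stop 27% of trials.

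Other conventional choices, also illustrative, lie far above −3.35. With 1350 per group and an effect of 0.35, O'Brien-Fleming-type beta-spending gives Z of about −0.40 (beta 0.08) to +0.41 (beta 0.20). Stopping when conditional power is below 20% gives about −1.13 under the 0.35 effect and +0.83 under the current trend.

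**6. The two triggers.** T2 is 30 days after enrolment, and planned accrual is 5 hospitals × 200 = 1000 a year. The two triggers then differ by about 1000 × 30/365 = 82 patients, under 3% of 3000.

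**The case against.** **Other routes to stopping exist.** A reader might infer that a trial with no effect must run to 3000 patients, or that the DSMB would be told futility had been assessed when it had not. The documents do not support either inference. The sponsor may stop for futility at any time, and that power is not tied to −3.35. The DSMB sees semi-annual reports under a charter with its own stopping rules, which is not shown. This limits the consequence. It does not make the published number match its published meaning.

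**The inference at the end is intact.** The rule does not inflate type I error, bias the estimate or alter the final analysis. The sample size was set mainly for secondary outcomes, so continuing past a flat SPPB result still yields useful data. That is so, but the interim section itself says the trial should stop if mobility cannot be improved.

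**Perhaps −3.35 tests against a benefit of 0.54 rather than 0.** Under that reading the rule would stop about 47% (540 per group) to 55% (600 per group) of no-effect trials. Nothing in the text suggests it: the boundaries are given as a symmetric O'Brien-Fleming pair for the primary comparison.

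**A real futility bound is a design decision, not just wording.** This stands. Z ≤ 0 is one choice among several, and a trial that it stops also stops collecting disposition, complication and cost data.

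**The trigger difference is small.** This stands too. Anyone who has reached T2 has already passed the time at which the T1 SPPB is due, so the two sections can be read together.

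**Conclusion.** The label and the stated interpretation of −3.35 are wrong as written. The number is a valid lower rejection bound, for harm, at 40% information. Crossing it requires an observed deficit of about 0.52 to 0.55 SPPB points. This numeric rule would stop 0.04% of trials with no effect and about 4% to 5% of trials with a true harm of 0.27 points, so it does not do the job that the section gives it.

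These figures assume the protocol's SD of 2.7, equal groups of 540 to 600 evaluable at the look, and a Z test of no difference. The conclusion concerns this rule only. Whether a null trial would in fact be stopped early also depends on the sponsor's discretion and on the charter. The mismatch in triggers is minor.

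**What to change.** 1. In *Interim analyses {21b}*, relabel ±3.35 as the efficacy and harm bounds, and remove the statement that crossing the lower one shows a failure to improve mobility. This is a wording change only.
2. State a separate, non-binding futility criterion that matches the declared intent, or refer explicitly to one in the DSMB charter. The sponsor and DSMB should choose the exact bound before the interim data are seen. Interim Z ≤ 0 on the SPPB comparison is one example: it stops 50% of no-effect trials and costs about 0.3, 0.7 and 1.0 percentage points of primary-outcome power at true effects of 0.432, 0.35 and 0.28. A non-binding bound does not inflate type I error. The further cost is that a stopped trial ends collection of the secondary-outcome data for which the sample size was chosen, and that should be weighed when the bound is set.
3. As a minor tidy-up, use one trigger in *Role of sponsor {5c}* and *Interim analyses {21b}*, for example 600 patients per group with the T1 SPPB due.
4. Carry the same wording into the DSMB charter.

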### Methods for additional analyses (e.g., subgroup analyses) {20b}

We will conduct three sensitivity analyses to account for (1) missing outcomes data, (2) treatment heterogeneity by site, and (3) the dose-response curve in the intervention group.

To identify the patients most likely to benefit from ambulating with a MT, we will build models separately for each treatment arm to predict the outcome of at least 1-point increase in the SPPB (i.e., beyond the minimal clinically important difference). Using the predicted probabilities resulting from these models, we will develop a Classification and Regression Tree (CART) that should identify subsets of patients likely to benefit, not benefit, or be harmed by the treatment. For example, the analysis might show that female patients aged >75 years who have an initial 6-Clicks score between 16 and 18 have an estimated treatment benefit of being 22% more likely to achieve the 1-point increase in SPPB. Essentially the tree will form risk groups of patients with shared characteristics that should receive a similar care recommendation.

We will estimate the total cost of the episode of care including the index admission (from hospital cost accounting systems) and all non-medication costs for the 30 days following enrollment (from Medicare claims) for all patients. For the intervention group, we will add the personnel costs for the MTs (hourly wages plus benefits). Since cost data are skewed, our cost estimates will be transformed and then compared between groups using the *t*-test.

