Many potential limitations for our study are mitigated by the study’s design. For example, patients who are enrolled may be unable or unwilling to ambulate three times each day. If adherence is lower than expected in interim analyses, we will compare adherence rates across sites and attempt to identify and spread best practices. If that is not successful, we would still likely have sufficient power to detect a difference in our primary (>99% power with 70% adherence) and secondary outcomes (80% power with 70% adherence). Depending on the ease of enrollment, we may decide to enroll additional patients with the same resources. We anticipate heterogeneous patients, sites, and controls. Given our large sample, we anticipate that all of these important covariates will be balanced between the intervention and control arms. If we find that they are not, we will adjust our outcomes for important confounders. If we are unable to directly identify subgroups for whom the intervention is most beneficial, we will create a score, based on logistic regression, to identify patients who benefit if they score above a certain threshold. Alternatively, we will provide recommendations and tools to enable individual hospitals to incorporate our prediction model into the electronic health record and identify patients directly from the model.

While functional decline in the hospital is multifactorial, general out-of-bed mobility is a modifiable factor for many patients. This randomized controlled trial will test the effectiveness of MT-assisted ambulation on outcomes that matter to both patients and hospitals, including functional status, hospital discharge disposition, and the incidence of potentially avoidable hospital complications. It will also provide a useful estimation of cost implications to help hospital administrators assess the feasibility and utility of creating MT positions in their own hospitals.

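### As described, the Aim 2 tree would almost always show subgroups of differing benefit even if the effect were uniform, and the plan states no option to conclude that benefit does not differ

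*Protocol article*

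**What the plan says.** Identifying which patients are more likely to benefit is one of three primary aims (Protocol article, Objectives {7}). The method is in Methods for additional analyses {20b}:

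- "we will build models separately for each treatment arm to predict the outcome of at least 1-point increase in the SPPB".
- The predicted probabilities from these models are used to develop a CART, which "should identify subsets of patients likely to benefit, not benefit, or be harmed by the treatment".
- In the worked example, women over 75 with low 6-Clicks scores "have an estimated treatment benefit of being 22% more likely to achieve the 1-point increase in SPPB". The tree is said to form "risk groups of patients with shared characteristics that should receive a similar care recommendation".

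The Discussion adds: "If we are unable to directly identify subgroups for whom the intervention is most beneficial, we will create a score, based on logistic regression", to be applied with a threshold. As an alternative, hospitals would be helped to "incorporate our prediction model into the electronic health record and identify patients directly from the model". The Discussion also announces in advance that a clinically useful classification model will result. The only weakness it names for the heterogeneity analysis is that it is observational and open to confounding.

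**The concern.** The worked example describes a treatment benefit, so the quantity of interest must be the predicted probability under treatment minus that under control. When two models are fitted independently, this difference carries the estimation error of both. A tree grown on it will split on that error. If the leaf effects are then read from the same patients, chance differences appear as differential benefit.

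The article describes no step that asks whether heterogeneity exists, and its stated response to finding no subgroups is another targeting rule. The output is meant to guide which patients get a mobility technician. A spurious leaf with little or negative predicted benefit could steer the service away from patients who gain as much as anyone else.

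**Working it through.** **Inputs from the article.** N = 3,000, 10% dropout, SD of SPPB change 2.7, and effects of 0.54 points (the MCID) and 0.35 points (Sample size {14}). Allocation is 1:1. Analysed: 3,000 × 0.9 = 2,700, or 1,350 per arm.

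**The plan's own figure.** Aim 2 has no stated power or error rate. The primary-outcome figure confirms the inputs. SE = 2.7 × √(2/1,350) = 0.104. For 0.54 points, 0.54/0.104 = 5.20, which gives 99.9% power. Diluting by 20% non-compliance (0.432 points) gives 98.6%. Both agree, to within rounding or nearly so, with the stated >99%.

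**How much noise the arm models create.** With p covariates in a logistic model per arm and response probability π, the SD across patients of the predicted difference under a uniform effect is about √(2·p·π(1−π)/n per arm). I assume π(1−π) ≈ 0.25.
- p = 10: √(2 × 10 × 0.25/1,350) = 0.061. Simulated: 0.057.
- p = 20: √(2 × 20 × 0.25/1,350) = 0.086. Simulated: 0.083.

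So a spread of 6 to 8 percentage points arises with no true heterogeneity at all.

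**Simulation.** Assumptions, since the article gives none: 10 or 20 baseline covariates, a few of them prognostic; control response about 45–50%; one logistic model per arm; a regression tree on the predicted difference (depth at most 3, each leaf at least 5% of patients, complexity parameter 0.01); 400 trials per scenario; everything on one dataset. Ranges run over 10 and 20 covariates.

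| Uniform true effect | Leaf gap ≥10 points | Any leaf below zero |
|---|---|---|
| None | 94–100% | 100% |
| 3-point risk difference | 94–100% | 95–99% |
| 0.35 SPPB points (about 5 risk points) | 95–100% | 82–93% |
| 0.54 SPPB points (about 8 risk points) | 94–100% | 53–68% |
| 8-point risk difference | 94–100% | 47–71% |

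The tree split in every trial, with between 7.6 and 7.8 leaves on average. A gap of at least 22 points, the size of the article's example, occurred in 6–20% of trials. The fixed risk-difference rows matter because a uniform shift in SPPB points need not be a uniform risk difference once the outcome is cut at 1 point. The pattern is the same on both scales.

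**Other learners (15 covariates).**
- Lasso, 60 trials: split in 95–100%; gap of at least 10 points in 80–85%; a leaf below zero in 95% with no effect and 45% at 0.54 points.
- Random forest, 40 trials: split in 100%; gap of at least 10 points in 88–93%; a leaf below zero in 100% with no effect and 33% at 0.54 points.

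**Would routine tree validation catch it?** No. The tree's cross-validated R² was 0.37–0.62 and above zero in every trial. Its target is a noise-free function of the covariates, because the noise entered earlier, in the arm models. Nor does it help to recompute the raw difference in the same patients. In 150 trials with 15 covariates and a uniform effect of about +5.7 points, the best leaf averaged +15.0 by prediction and +15.0 raw. The worst averaged −3.8 and −4.0, where the true effect was +5.6.

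**What does catch it?** With a 50/50 split, the apparent leaf gap in the training half was 26–27 points (larger than above because each arm model has half the patients). In the held-out half the same leaves differed by 0.3–0.4 points on average. A global treatment-by-covariate test rejected in 3–5% of uniform-effect trials.

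**The case against.** The strongest reply is that this is a condensed article. Learner, tuning, pruning and validation belong in an analysis plan that is not shown. The article says neither that everything is done on the same patients nor that the two predictions are subtracted. The first point stands: single-dataset use is inferred from silence, and the held-out result shows how much depends on it. The second is weaker, because the worked example makes sense only as a contrast between arms.

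The numbers also depend on settings that the article does not fix. A reader might infer that the method is bound to report harm. The documents and the calculations do not support that. At an MCID-sized uniform effect, a leaf below zero appears in roughly one third to two thirds of trials, depending on the learner. The article sets no cut-off for harm, and a slightly negative leaf could be placed in its no-benefit class.

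A reader might also infer that the plan forbids a null conclusion. It does not; it omits one. The fallback sits in a Discussion paragraph on mitigating limitations, and its trigger could mean only that the tree gave no usable groups. The fallback was not simulated, and a tree that always splits might never trigger it.

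What remains is stated text: separate arm models feeding a tree, leaves tied to care recommendations, and a fallback that names further targeting tools but no null result. The caution about confounding does not cover false subgroups.

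**Conclusion.** The concern holds in this form. Run as written on one dataset, the procedure almost always shows leaves of differing benefit when the effect is the same for everyone, and it often shows a leaf with predicted effect below zero. How often depends on the true average effect and the learner: about 100% of trials with no effect, 82–93% at 0.35 SPPB points, 53–68% at 0.54 points with logistic arm models, and 33–45% at 0.54 with random forest or lasso. These figures rest on 2,700 analysed patients and on assumed covariates, prognostic strength and tree settings. The direction was the same in every variant tried.

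The finding is not that harm will certainly be reported, nor that a null result is ruled out. It is that the described method has no stated protection against false subgroups, and the text provides no route to saying that none were found. For a primary aim this should be corrected before the analysis is run.

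**What to change.** In Methods for additional analyses {20b}:
- Obtain each patient's predicted benefit by cross-fitting or sample splitting.
- Estimate each leaf's effect, with a confidence interval, from the randomised comparison in patients not used to build the models or the tree.
- Prespecify one global test of heterogeneity on a named scale (risk difference, odds ratio or SPPB points).

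The particular split, such as leaving out one hospital at a time, can be left to the statistician.

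In the Discussion, make the threshold score or health-record model conditional on that held-out evidence, and state that no evidence of differential benefit will be reported otherwise.

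The cost is more analysis code, less extreme leaf estimates and wider intervals; no new data are needed. For example, take a leaf holding 20% of patients and a 95% half-width of 1.96 × √(2 × 0.25/m), with m patients per arm. On the full data m = 270, giving ±8.4 points. In a held-out half m = 135, giving ±11.9 points.
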